#### 3.1.3 Participants:

Inclusion Criteria:

(1) Patients diagnosed with gastric cancer through pathological examination.

(2) Age  $\geq 18$  years.

(3) Patients who have undergone their first gastric cancer surgery and plan to undergo chemotherapy at the research hospital, with follow-up conditions.

(4) Patients whose condition allows for participation, who have provided informed consent, and are cooperative.

(5) Patients with an expected survival period of more than six months.

Exclusion Criteria:

(1) Patients with communication and understanding impairments.

(2) Patients with other severe diseases.

(3) Patients with a history of psychological disorders or mental illness.

(4) Patients currently participating in other clinical studies.

Dropout Criteria: Patients who, for various reasons, do not complete the entire resilience intervention program.

3.1.4 Sampling Method: Convenience sampling.

3.1.5 Sample Size Calculation: Sample size was calculated using G\*Power software. Based on the pilot study results and the estimated effect size for the primary outcome measure, psychological resilience, and accounting for a 10% dropout rate, the final sample size is determined to be 196 participants, with 98 in the intervention group and 98 in the control group.

3.1.6 Data Management and Analysis: Data will be double-entered using Epidata 3.1, and analyzed using IBM SPSS 24.0 software. Statistical significance is set at  $P \leq 0.05$ . Quantitative variables with normal distribution will be compared using independent sample t-tests, while non-normally distributed variables will be analyzed using the Wilcoxon rank-sum test. Qualitative variables will be compared using the chi-square test.

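### The normality of the trial data decides whether resilience, the primary outcome, is compared by means or by ranks; one analysis should be named in advance

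*Combined protocol and SAP*

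**What the plan says.** Section 3.1.6 (Data Management and Analysis) gives one rule, with two branches, for all quantitative variables. The first branch reads: "Quantitative variables with normal distribution will be compared using independent sample t-tests". The second branch, for everything that fails the unstated normality criterion, reads: "while non-normally distributed variables will be analyzed using the Wilcoxon rank-sum test". The significance level is P ≤ 0.05, with sidedness not stated.

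Section 3.1.5 identifies the primary outcome when it describes the basis of the sample size as "the estimated effect size for the primary outcome measure, psychological resilience". It allows for 10% dropout and gives the resulting total as follows: "the final sample size is determined to be 196 participants, with 98 in the intervention group and 98 in the control group".

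The visible text does not say how normality is to be judged (test, threshold or plot; each arm or pooled), what effect measure will be reported, or that resilience is exempt from the general rule. The rule therefore covers the primary outcome.

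**The concern.** The two tests answer different questions. The t-test concerns a difference in mean resilience. The rank-sum test concerns whether scores in one arm tend to exceed those in the other. Under this rule, a feature of the observed sample decides which question the trial answers.

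Three things follow:

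- The hypothesis and the reported effect are not fixed before the data are seen. Two samples from the same population can lead to different primary analyses.
- If the rank-sum branch is taken, the test gives no mean difference with a confidence interval, and the plan provides no other effect estimate.
- If readers take the result as a statement about means, the rank-sum branch does not guarantee the 5% level when the arms differ in spread or shape. That could happen if the programme helps some patients much more than others.

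**Working it through.** **Inputs from the plan (sections 3.1.5 and 3.1.6).** 98 per group, 10% dropout, significance at P ≤ 0.05, t-test if normal and Wilcoxon if not. Evaluable per group: 98 × 0.90 = 88.2, about 88.

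**The plan's own figure.** The effect size and power behind 196 are not stated, so the figure can be neither confirmed nor refuted. It is compatible with ordinary inputs. With n = 2(z₀.₉₇₅ + z_power)² / d² per group:

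- Assumed d = 0.424, 80% power: 2 × (1.960 + 0.842)² / 0.424² = 15.70 / 0.1798 = 87.3, so 88. Then 88 / 0.90 = 97.8, so 98 per group and 196 in total.
- Assumed d = 0.49, 90% power: 2 × (1.960 + 1.282)² / 0.49² = 21.0 / 0.2401 = 87.5, so again 88, 98 and 196.

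An exact t-test calculation gives 89, then 99 per group, for the same inputs.

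**Assumptions for the simulations (not in the plan).** 88 per arm; two-sided 5%; Shapiro-Wilk at 5% in each arm; t-test if both arms pass, otherwise Wilcoxon. Bounded scores are Beta variables × 100, rounded.

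**Step 1: how often the rule switches.** Both arms share one distribution. The ranges cover three runs, of 3,000, 10,000 and 5,000 trials per case.

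| Distribution | Skewness | At least one arm called non-normal |
|---|---|---|
| Beta(5,3) | -0.31 | 47% to 49% |
| Beta(6,3) | -0.41 | 65% to 66% |
| Beta(4,2) | -0.47 | 90% to 91% |

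Small differences in skewness move the rule from an even split to almost always Wilcoxon.

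**Step 2: type I error with identical arms.** In the three Beta cases the two-stage rule rejects in 4.9%, 5.5% and 5.1% of 10,000 trials. In seven further cases (20,000 trials each, Monte Carlo standard error about 0.15 percentage points) it rejects in 4.8% (normal), 5.3% (rounded 0-100 score), 5.0% (ceiling-limited), 5.2% (gamma, shape 16), 5.0% (gamma, shape 4), 5.1% (lognormal) and 5.3% (exponential). This is essentially nominal.

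**Step 3: equal means, unequal spread.** Beta(8,4) against Beta(3,1.5), both × 100.

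- Means: 8/12 = 3/4.5 = 0.667, so 66.7 in each arm.
- SDs, from √[ab / ((a+b)²(a+b+1))]: √(32/1872) = 0.131 and √(4.5/111.4) = 0.201, so 13.1 and 20.1. Variance ratio about 2.4.
- Rejection over the three runs: two-stage rule 9.2%, 9.7% and 8.8%; Welch's test 5.0%, 5.1% and 4.4%.

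**Step 4: equal means and variances, different shape (20,000 trials).**

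| Normal arm against | Two-stage rule | Fixed t-test |
|---|---|---|
| gamma, shape 16 | 6.0% | 5.2% |
| gamma, shape 4 | 8.1% | 5.1% |
| exponential | 14.6% | 5.2% |

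**Step 5: does the mean comparison need protecting?** The fixed t-test's error is 4.7% to 5.4% in the Beta cases of Step 1 and 4.7% to 5.2% in all ten cases of the 20,000-trial run, including skewed and ceiling-limited scores. With equal arm sizes, the Student and Welch statistics coincide and only the degrees of freedom differ.

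**The case against.** The strongest counter-argument is that the rule is common practice and does little harm. If the programme has no effect at all, both arms share one distribution, and Step 2 shows a rate close to 5%. In Steps 3 and 4 the distributions really differ, so a rank-test rejection is correct for its own hypothesis. It is an error only if equality of means is the target. All of this stands. A reader might infer that the plan's error rate is uncontrolled in general; neither the document nor the calculations support that.

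A reader might also infer that the choice of test is a coin toss. That fits only the mildest skew tried, and a plot or a skewness threshold would switch at another rate.

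A third tempting reading is that the analyst will look at both P values and then judge normality. Nothing in the document suggests this. Even if the smaller P value were always taken, identical arms would give 5.6% to 6.0% in the Beta cases and 5.7% to 7.3% in the others.

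Nor can it be said that the rank test departs from the scale used to size the trial. Section 3.1.5 names G\*Power and a pilot effect size but no test family or metric, and that software can size either test.

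Finally, the available text of section 9 breaks off as it returns to data management, and the flowchart is not shown, so further detail there could not be checked. None of these points fixes the primary hypothesis or the effect to be reported, which is what the visible rule leaves to the data.

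**Conclusion.** The point holds in a limited form. As written, section 3.1.6 lets the trial data choose the hypothesis and effect measure for resilience, by an unstated criterion. This is chiefly a weakness in what is estimated and reported. The error-rate consequence is conditional: none of note with identical arms and a fixed check; about 9% against about 5% for Welch's test in one assumed equal-means, unequal-spread scenario; 6.0% to 14.6% when only shape differs. These sizes rest on the assumed scales, distributions and Shapiro-Wilk check, since the document gives no instrument, range, SD or normality check. The reading of the rule itself rests on none of them. The change is worth making but is not critical.

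**What to change.** Add to section 3.1.6, for the primary outcome: *Psychological resilience will be compared between groups as a difference in means with a 95% confidence interval, using Welch's t-test, regardless of the distribution of the scores. The Wilcoxon rank-sum test will be reported as a sensitivity analysis only.*

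If a baseline resilience score is collected, a linear model adjusted for it may be named instead of Welch's test. The visible text describes no such measurement, so this option is conditional. Whichever is chosen should be fixed before outcome data are examined.

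The cost is a short addition to the text: no extra data, no patient burden and no change to the 196 participants. The downside is slightly less power than a rank test if the scores turn out heavily skewed.

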### 3.2 Qualitative Research:

#### 3.2.1 Participants:

Participants will be purposively sampled from the intervention group of the

empirical study, following the principle of maximum variation, selecting patients with diverse ages, educational backgrounds, occupations, and exercise habits. The sample size will be determined by data saturation, i.e., when no new themes emerge.

### 3.2.2 Data Collection and Analysis:

Semi-structured interviews will be conducted after informing the participants about the purpose and methods of the interviews and obtaining their informed consent. Interviews will be recorded, anonymized, and transcribed verbatim. Data will be organized and analyzed using Nvivo 11.0 software, with statistical descriptions of participants' sociodemographic characteristics and thematic analysis of interview data using Colaizzi's seven-step phenomenological method.

### 3.3 Evidence Summary:

#### 3.3.1 Literature Sources:

The study will retrieve evidence on resilience enhancement in cancer patients from databases including BMJ Best Practice, UpToDate, Cochrane Library, JBI Evidence-Based Healthcare Center, International Guideline Network, Scottish Intercollegiate Guidelines Network, National Comprehensive Cancer Network, Registered Nurses' Association of Ontario, European Society for Medical Oncology, American Society of Clinical Oncology, Italian Society of Medical Oncology, PubMed, Web of Science, and Chinese databases such as CNKI, Wanfang Data, VIP, and Chinese Biomedical Literature Database. The search will cover literature published up to December 2023, with core search terms including "cancer," "resilience," and their synonyms or variations.

#### 3.3.2 Research Methods:

Different quality assessment methods will be applied based on the type of research included. The quality assessment process will be independently conducted by two researchers, and any discrepancies will be resolved through consultation with a third party until consensus is reached.

## 4. Study Implementation Process

Flowchart:

## 5. Risk/Benefit Analysis

Benefits:

This study aims to enhance the psychological resilience of patients, improving their quality of life. If successfully conducted, the study can provide valuable insights for developing resilience intervention programs for other chronic disease patients.

Risks:

For patients, this study involves a non-invasive resilience intervention for eligible participants. Professional healthcare personnel will provide care during the intervention, and patients can withdraw at any time during the study. All researchers have undergone standardized training.

## 6. Participant Recruitment and Protection Measures

### 6.1 Recruitment:

Inclusion Criteria:

- (1) Patients diagnosed with gastric cancer through pathological examination.
- (2) Age  $\geq 18$  years.

(3) Patients who have undergone their first gastric cancer surgery and plan to undergo chemotherapy at the research hospital, with follow-up conditions.

(4) Patients whose condition allows for participation, who have provided informed consent, and are cooperative.

(5) Patients with an expected survival period of more than six months.

Exclusion Criteria:

(1) Patients with communication and understanding impairments.

(2) Patients with other severe diseases.

(3) Patients with a history of psychological disorders or mental illness.

(4) Patients currently participating in other clinical studies.

Dropout Criteria: Patients who, for various reasons, do not complete the entire resilience intervention program.

#### 6.2 Protection Measures:

Participants will be informed of all relevant information about the study and its progress, allowing them to decide voluntarily whether to continue participating. Participants may withdraw from the study at any time without affecting their medical care or rights. If continuing in the study poses a significant risk, the study will be terminated. During the study, participants can report any discomfort to the research team.

### 8. Costs, Compensation, and Potential Compensation for Study-Related Harm

All technical and material costs associated with this clinical study (including material printing costs) will be covered by the project funds. There will be no additional financial burden on the participants. During the study, small gifts may be provided to participants as a reward, funded by the project. The patients and their families are the direct beneficiaries.

### 9. Data Collection, Management, and Quality Control

Data Management and Analysis:

Data will be double-entered using Epidata
